### Phase 1: Process Mapping

#### Study Design

We will perform process mapping [66,67] via direct clinical observation of the pCGA visit, qualitative interviews with patients, and a focus group with staff, using SEIPS as a framework [60,67,68]. Process mapping is a fundamental systems engineering approach based upon the recognition that work, as it is performed in real-world settings, is not always consistent with its expected or prescribed form. We expect that phase 1 will catalog components of the SEIPS-based work system (traditional process map), and we will supplement the map by identifying barriers and facilitators to each step.

#### Participants

##### Patients and Caregivers

Eligible participants are patients aged ≥85 years or those aged ≥65 years with multiple comorbid conditions (>2), diagnosed or suspected cognitive impairment, diagnosed or suspected functional impairment, or poor nutrition (documented weight loss of 10% within a year). Inclusion criteria are older adults for whom the surgeon recommends an operative intervention and who intend to undergo the elective major abdominal surgery. Exclusion criteria are non-English speakers (because we do not have the resources for translation) or the absence of a caregiver for those without decisional capacity. On the basis of prior literature [68], we will enroll 20 older adults and their caregivers, if present, for observation and interviews. We will use purposive sampling to recruit at least 2 patients each for groups traditionally underrepresented in medical research by race, ethnicity, socioeconomic status, and rural or urban backgrounds [69]. Research staff will screen patients for eligibility. Clinic staff will approach participants to assess interest, and research staff will obtain informed consent.

##### Health Care Professionals and Staff

All health care professionals working in the preoperative geriatric clinic (n=10) who are responsible for performing the tasks of the pCGA will be approached and consented for direct observation and focus groups to provide feedback on the pCGA process map. Additional staff (n=5) engaged in the clinic (administrative leads and schedulers) will be invited to participate. We will invite referring surgeons (n=10) for one-on-one interviews, with the plan to recruit additional participants as informed by thematic saturation during the ongoing analysis. We will purposively select surgeons, men as well as women, to represent a range of surgical specialties. Recruitment will occur by email for health care professionals.

#### Predicted pCGA Process Map

The pCGA clinic is conducted after the initial surgical consultation and before the surgical operation. A predicted map of the existing process is outlined in Figure 2. The patient consults with a surgeon who recommends an operative intervention and places a referral for the pCGA clinic. The pCGA is conducted at 2 locations and provides web-based options for patients traveling from a distance. The pCGA results include recommendations for patient-level tasks (exercises and nutritional shakes), provider tasks (medication changes), or additional preoperative evaluation.

**Figure 2 figure2:**

Predicted process map of patient journey through the preoperative comprehensive geriatric assessment (pCGA). Each point along the process will be evaluated using the systems engineering initiative for patient safety to identify key work tasks and associated barriers. Research activities are noted in blue italics.

#### Data Collection

##### Direct Observation

We will embed a trained research assistant at the clinic and use direct observation guided by a fidelity checklist to document the events of the pCGA and take notes on the process. We will follow the patient from initial check-in through the completion of the visit, providing a detailed and direct account of the patient’s journey [66]. The observers will use a standardized template to document the persons, tasks, tools and technology, environment, and organizational factors according to the SEIPS model. Observer notes will be supplemented with an audio recording of the patient-physician interaction.

##### Interviews

We will interview patients and caregivers 2 weeks after the pCGA visit. Research staff trained in qualitative methods will conduct the interviews using a semistructured interview guide to elicit feedback on the predicted process map (Figure 2). The interview probes will assess barriers, facilitators, motivation, and adherence to patient work tasks, as well as reflections on the process of scheduling, attending, and participating in the pCGA. We will conduct interviews using a virtual platform. The interviewer will ask the patient to visually show on screen the home environment and ask probing questions to gain a more in-depth understanding of how tasks are performed. We expect each interview to last 45 minutes. We will interview surgeons using semistructured guides to elicit feedback on the process map and any barriers or facilitators according to the SEIPS model. The interview will provide an understanding of perceived barriers and facilitators to the adoption of the pCGA and explore how the surgeons’ separate workflow fits into the proposed process map. Surgeon interviews are expected to last 45 minutes.

##### Focus Groups

Qualitative research staff will engage pCGA health care professionals and staff (n=10) in a focus group after completing direct observations. Focus groups naturally foster within-group interactions, allowing us to gain additional insight into the accuracy of the process map from multiple perspectives. A semistructured guide based on the SEIPS model will elicit feedback on the process map, clarifying its accuracy as a representation of the tasks and procedures performed and identifying system-level barriers and facilitators at each step. The focus group will be audio recorded and is expected to last 90 minutes.

#### Data Analysis

##### Qualitative Analysis

The interview and focus group audio recordings will be transcribed and analyzed using a deductive strategy [70,71] and the SEIPS framework to develop the coding taxonomy, with a focus on identifying barriers and facilitators within each SEIPS category for each step. Our analysis will use triangulation, comparing observed data points from the pCGA visit to those from the patient interviews. The transcripts will be coded independently by 3 researchers, followed by a joint discussion to explore disagreement and achieve consensus. We will use qualitative analysis software NVivo 14 (Lumivero) to catalog coded data.

##### Process Mapping

The aforementioned qualitative analysis and direct observations will be used to adapt the SEIPS-based process map [68]. We will supplement the map with a table, cataloging individual tasks in rows, numbered in reference to the map, with columns listing the persons, environment, and tools and technology, as well as the barriers and facilitators to the completion of each task.

### Phase 2: Participatory Design

#### Study Design

In phase 2, we will apply user-centered participatory design methods to adapt the process map (phase 1) into an implementation package, consisting of a set of implementation strategies, to address barriers and enhance facilitators at each step. Participatory design [72] is a systems engineering method where researchers and participants work together to design the workflow of an intervention. Co-design sessions will be conducted in parallel at a large quaternary academic medical center and an affiliated community-based hospital. There will be 2 groups (design teams) of patients and caregivers and health care professionals per location (a total of 4 groups).

#### Participants

##### Overview

Each design team will consist of 7 participants. As participatory design aims for solution convergence, having an odd number of participants facilitates tie-breaking within groups. The small number of stakeholders in each group, as opposed to 14 in 1 group, allows all stakeholders to provide their input and facilitates critical evaluation.

##### Patients and Caregivers

Older adults are eligible after having completed the pCGA, followed by major abdominal surgery and subsequent recovery. We will approach patients and caregivers at each location (academic hospital and community-based hospital) with the goal to enroll 7 of them for participation. Patients and their caregivers will be approached at the follow-up surgical visit, which is conducted at 14 days postoperatively. Of note, older adults with Alzheimer disease or related dementias will be included if they provide assent and are accompanied by a caregiver who also consents and participates alongside them. We will use purposeful sampling to recruit at least 1 patient or caregiver from underrepresented groups by race, ethnicity, socioeconomic status, and rural or urban backgrounds [69]. We intend to oversample to ensure that perspectives from patients identified as vulnerable are heard.

##### Health Care Professionals

Eligible health care professionals will include surgeons performing major abdominal surgery whose patients may benefit from pCGA and health care professionals who conduct or could potentially conduct elements of the pCGA. For the academic medical center, this will involve the same set of health care professional participants as in phase 1. These include geriatricians, primary care providers, advanced practice providers, social workers, medical assistants, pharmacists, and physical therapists. We will also invite the participation of additional ancillary staff, such as administrative leads, schedulers, and tech support.

#### Data Collection

We will conduct 5 co-design videoconference sessions with each group over 6 months, with a gap of 2 to 3 weeks between each session (Textbox 1; during the periods between the sessions, input from the alternate design team will be synthesized for presentation to the next team and an analysis performed of prior session content). In session 1, we will present the process map generated in phase 1 and a prototype of the current pCGA implementation package. Researchers will facilitate the discussion, maintaining respectful debate among design team members as they identify process changes that will promote the implementation of the pCGA package. The facilitators will focus on solution convergence from session to session. Each design team will participate in sessions independently; however, we will summarize the output from each session and present it to the alternate design team for comment. Each session is expected to last 90 minutes. Sessions will be conducted virtually to promote participation and retention and audio recorded for qualitative analysis. Co-design sessions will be conducted separately for the academic hospital and the community-based hospital.

Outline of the participatory co-design sessions.
**Sessions and content for preoperative comprehensive geriatric assessment (pCGA) implementation redesign**
Methods introduction, process map review, initial implementation package designRefinement of inputs (eg, referrals)Refinement of pCGA system workflows (eg, telephone calls)Refinement of pCGA output and feedback mechanismsFinalizing implementation package, rollout planning

#### Data Analysis

Qualitative data analysis of the design sessions will be performed using the rapid identification of themes from audio recordings method [73] to facilitate rapid iterative refinement of the implementation package between sessions. After each session, the research team will analyze audio recordings directly without transcription, identifying key themes, an initial codebook, and preliminary analysis of codes. We will synthesize these findings with outputs from the design session, such as sketches, case scenarios, ratings, research team observation notes, and stakeholder notes. This allows early identification of key themes after each session that can then be provided back to stakeholders in the subsequent session. Data analysis will focus on identifying implementation strategies to mitigate perceived barriers or strengthen known facilitators (Textbox 2). We will investigate novel solutions as well as known implementation strategies, such as the 73 discrete strategies delineated in the Expert Recommendations for Implementing Change [74,75].

Examples of potential implementation strategies based on the systems engineering initiative for patient safety (SEIPS) categories to improve reach and adoption while maintaining fidelity.
**SEIPS categories and possible strategies**
People: dedicated referral coordinator (or registered nurse) within surgical clinicsOrganization: clear parameters for referral and script for telephone triageTools: telehealth for remote patients, educational handouts, and order setsTasks: automate recommendations to primary care or referring providerEnvironment: travel vouchers for patients with limited transport

### Phase 3: Pilot Trial of the pCGA Implementation Package

#### Study Design

We will conduct a pretest-posttest pilot study of the implementation package over 10 months, conducted at the clinic level at 2 busy academic medical center surgical subspecialty clinics performing major abdominal surgery (selecting one that does not routinely refer for pCGA in addition to one that does routinely refer). We will collect baseline prepilot data via retrospective chart abstraction from the year before the intervention. After an implementation rollout period of 2 months, postintervention data will be collected over 10 months. Specifically, we will assess outcomes according to the RE-AIM framework [38], using chart abstraction for patient-level data and simple self-reported surveys for the health care professionals. We hypothesize that a user-designed implementation package will improve the reach and adoption of the pCGA compared to the historic baseline.

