### Ethical Considerations

The study will be conducted in 3 phases. Each phase will be reviewed separately by the institutional review board (IRB) of the University of Wisconsin–Madison. Phase 1 of the study was approved by the IRB on January 19, 2023 (2022-1516). All participants provide informed consent for both observations and interviews. To protect privacy and confidentiality, all data are deidentified. Compensation is provided in the form of gift cards. Participants receive US $20 for participating in observations and US $20 for a 45-minute qualitative interview. Health care staff receive US $45 for a 90-minute focus group. Surgeons receive US $50 for a 45-minute interview. Phase 2 of the study was approved by the IRB on March 1, 2024 (2024-0044). All participants provide informed consent. To protect privacy and confidentiality, all data are deidentified. Compensation is provided in the form of gift cards. Patient and caregiver participants receive US $50 per 90-minute session. Health care professionals receive US $100 per 90-minute session. Phase 3 study activities will be initiated after receiving approval from the IRB. All participants will be required to provide informed consent. To protect privacy and confidentiality, all data will be deidentified. Compensation will be provided in the form of gift cards. Participants will receive US $5 per completed survey.

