#### Participants

##### Patients

Older adults presenting to surgical clinics will be screened for eligibility criteria by study staff. Eligible participants are patients aged ≥85 years or those aged ≥65 years with multiple comorbid conditions (>2), diagnosed or suspected cognitive impairment, diagnosed or suspected functional impairment, or poor nutrition (documented weight loss of 10% within a year). The inclusion criterion is eligible older adults planning to undergo elective major abdominal surgery. Exclusion criteria are non-English speakers (because we lack resources for translation) or the absence of a caregiver for those without decisional capacity.

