##### Recruitment and Enrollment

Clinic staff will approach potential participants to determine interest, and a study team member will then share study details and obtain consent. At baseline, 40 patients per year are seen for pCGA. We expect to enroll 20 patients over the pilot period. All patient data for the pilot will be obtained via chart abstraction. The study will be subject to IRB approval.

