#### Outcomes

The primary outcomes of this pilot trial will be reach and adoption, assessed using the RE-AIM framework [38] (Table 2). Reach refers to the percentage and characteristics of older adults receiving the pCGA intervention, while adoption accounts for those health systems and health care professionals who refer patients for, or deliver, the pCGA [38,92]. Of note, implementation in the RE-AIM framework refers to fidelity, or the extent to which an intervention is delivered as intended. We will expand the implementation domain to include measures of fidelity, as defined by NIH Best Practices [40], as well as feasibility, acceptability, and appropriateness according to the taxonomy of implementation outcomes developed by Proctor et al [93]. The primary effectiveness outcome will be postoperative length of stay, which is an easily measured, continuous outcome variable commonly used in the surgical literature on pCGA [29]. We will collect exploratory measures to inform the selection of effectiveness outcomes for a future implementation-effectiveness trial. These exploratory outcome measures will include (1) a composite of death or postoperative complication events; and (2) data points relevant to the pCGA, including a cognitive outcome (postoperative delirium), functional outcome (discharge destination to home, rehabilitation, or skilled nursing), nutritional outcome (discharge diet, albumin level, and weight at discharge), and polypharmacy (Beers criteria discharge medications [79], anticholinergic burden score [78], and number of opioid pain pills prescribed at discharge).

**Table 2 table2:** The reach, effectiveness, adoption, implementation, and maintenance (RE-AIM) domains and associated outcome measures.

Domain	Definition	Measurement
Reach	The percentage and characteristics of older patients who receive pCGA^a^ before abdominal surgery	Referred ÷ potentially eligible patients Comparison of referred ÷ eligible patients by age, sex, race, ethnicity, BMI, and zip code Target reach: >50% referral of eligible pCGA patients per clinic
Effectiveness	The improvement in clinical outcomes from pCGA receipt	Primary: postoperative length of stay Secondary: 30-day morbidity and mortality (refer to Chart Abstraction section)
Adoption	Surgeon intent, decision, and action to refer eligible patients for pCGA	Percentage of surgeons referring ÷ total surgeons in the pilot clinic Target adoption: >75% of surgeons achieving >50% referrals

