#### Data Analysis

The aim of the pilot is to maximize reach and adoption while maintaining implementation fidelity before a full-scale implementation-effectiveness hybrid trial is conducted. The limited sample size will restrict our ability to evaluate differences in effectiveness outcomes such as mortality or morbidity; however, more proximal effectiveness estimates will be explored by abstracting short-term clinical outcomes (eg, medication changes at discharge). We will use exploratory measures to establish some preliminary point estimates for event rates and CIs within our sample for the purpose of planning a future study. As such, formal power calculations are not applicable to this pilot study. Recruitment data will inform the calculation of the reach, adoption, and maintenance outcomes. We will explore all RE-AIM outcomes for differences across underrepresented groups [69] (rural vs urban as determined by zip code, racial majority vs minority groups, men vs women vs other gender identities, and Hispanic vs non-Hispanic ethnicity). All data will be entered into Stata software (StataCorp LLC) for analysis. Data will be evaluated for accuracy and missingness. Descriptive univariate and bivariate analyses will be conducted, including chi-square tests for categorical data and 2-tailed *t* tests or Mann-Whitney *U* tests for continuous data as appropriate, with a cutoff of *P*<.05 for statistical significance.

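### Reach and adoption are compared with a historic baseline, but eligible patients are identified from past charts before the package and by staff screening and recruitment records after it

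*Protocol article*

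**What the plan says.** Phase 3, Study Design, describes a pretest-posttest pilot in two surgical clinics and sets the comparison against a historic baseline. The only baseline source it names is the chart: "We will collect baseline prepilot data via retrospective chart abstraction from the year before the intervention".

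For the pilot period, Participants (Patients) says "Older adults presenting to surgical clinics will be screened for eligibility criteria by study staff". The criteria that open eligibility at age 65 or over include, besides more than two comorbid conditions, "diagnosed or suspected cognitive impairment, diagnosed or suspected functional impairment, or poor nutrition (documented weight loss of 10% within a year". Recruitment and Enrollment adds "Clinic staff will approach potential participants to determine interest, and a study team member will then share study details and obtain consent", and Ethical Considerations says of Phase 3 "All participants will be required to provide informed consent".

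Table 2 (Outcomes) measures reach as "Referred ÷ potentially eligible patients", with the threshold "Target reach: >50% referral of eligible pCGA patients per clinic". The adoption target requires more than 75% of surgeons to refer more than 50%. Data Analysis then states "Recruitment data will inform the calculation of the reach, adoption, and maintenance outcomes".

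Recruitment and Enrollment also says that patient data in the pilot come from the chart. Chart Abstraction describes trained abstractors, a data dictionary and audits of interrater reliability. Neither section says how the eligible denominator will be counted in each period. The Limitations section does not raise the matter.

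**The concern.** Reach is a proportion whose denominator is a count of eligible patients. If that count is made in one way before the package and in another way after it, the pre-post difference contains a change of measurement as well as any change in referral.

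The protocol's own rationale suggests why the two counts may differ. The Background says that functional decline, frailty and cognitive impairment are seldom assessed, and the Abstract says that function and cognition are often left out of routine preoperative planning. Table 1 shows that the pCGA is where they are tested. A past chart is therefore more likely to reveal impairment in a patient who was referred and assessed than in one who was not. Losing non-referred patients from the baseline denominator raises apparent baseline reach. One of the two clinics is chosen because it does not routinely refer, so the gap may also differ between clinics, while the reach target is set for each clinic.

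At stake is the pilot's main comparison, which will be tested at P<.05 and used to plan the next trial.

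**Working it through.** The protocol gives no baseline reach, eligible count or capture rate, so there is no stated figure to reproduce. Every capture rate below is an assumption.

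**Formula.** Let R be true reach, *a* the share of referred eligible patients that the method finds, and *b* the share of non-referred eligible patients that it finds. Then

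apparent reach = R·a / (R·a + (1 − R)·b).

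**Step 1: baseline from charts.** Take a = 1 and b = 0.5 to 0.9.

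| True reach | b = 0.9 | b = 0.7 | b = 0.5 |
|---|---|---|---|
| 20% | 21.7% | 26.3% | 33.3% |
| 30% | 32.3% | 38.0% | 46.2% |
| 40% | 42.6% | 48.8% | 57.1% |
| 50% | 52.6% | 58.8% | 66.7% |

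For example, 0.40 / (0.40 + 0.60 × 0.5) = 0.571. The overstatement runs from 1.7 to 17.1 points.

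**Step 2: effect on the comparison.** Suppose post-period screening is complete and true reach stays at 30%. The apparent change is then −2.3, −8.0 or −16.2 points for b = 0.9, 0.7 or 0.5. If true reach rises from 30% to 50%, a gain of 20 points, the apparent gain is 50 − 32.3 = 17.7, 50 − 38.0 = 12.0 or 50 − 46.2 = 3.8 points.

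**Step 3: chance of a false signal.** Assume 100 truly eligible patients in the 12 baseline months and 83 in the 10 pilot months, with true reach of 30% in both. An approximate calculation for two proportions gives a 5%, 19% or 52% chance of P<.05 for b = 0.9, 0.7 or 0.5. The apparent direction is a fall in reach.

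**Step 4: adoption.** A surgeon who truly refers 40% appears to pass 50% when 0.40 > 0.60·b, that is, when b < 0.667. Adoption inherits the error through the per-surgeon 50% threshold.

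**Step 5: conditional opposite bias.** This arises only if the post-period denominator is limited to consented patients. Assume that 90% of referred patients consent, that 50%, 70% or 90% of non-referred patients consent, and that the baseline is complete. True reach of 30% then reads as 43.5%, 35.5% or 30.0%, a false gain of 13.5, 5.5 or 0 points.

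**Step 6: same rule in both periods.** With the same a and b before and after, the apparent change is 0 when true reach is constant. With a = 1 and b = 0.7 throughout, a true rise from 30% to 50% reads as 38.0% to 58.8%, a gain of 20.8 points. The level is still off, but the change is close to the truth.

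**The case against.** The strongest reply is that patient data in the pilot come from charts in both periods, under a data dictionary with audited abstraction. Staff screening could itself be chart review, and a journal article need not spell out every operational rule. Part of this stands: the article does not say how staff screen, and it does not say in words how baseline eligibility is found. But the chart-abstraction sentence covers data collected on patients. It does not say that the pilot denominator will be rebuilt by the baseline rule, and the screening and recruitment-data statements point the other way. Analysis cannot supply screening that was not done in the baseline year.

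A second reply is that several routes to eligibility need no pCGA visit: age 85 or over, comorbidity count and documented weight loss. This stands. Only patients who qualify solely through suspected or uncharted impairment are at risk of being missed, so 50% capture is a severe case.

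Some stronger readings are tempting but not supported.

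- A reader might infer that the study approach acts as a referral prompt outside the package. The article does not say whether the approach comes before or after referral, and the package is not yet designed.
- A reader might infer that reach counts only consenting patients. Table 2 uses potentially eligible patients, and recruitment data may mean screening counts.
- A reader might infer that length of stay will compare volunteers with unselected patients. Results (Phase 3) speaks of enrolling patients in the preimplementation period too, so their consent status is unclear.
- A reader might infer that baseline inflation helps the package to meet the 50% reach target. A target judged on post-period reach is unaffected by the baseline count.

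**Conclusion.** The concern holds as a mismatch in how the denominator of a primary outcome is counted in the two periods. It rests on retrospective abstraction being the only baseline source named, on the pilot using staff screening and recruitment data, and on the absence of a stated common rule.

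The direction suggested by the protocol's own rationale is an overstated baseline, which works against the package. Under the assumed capture of 50-90%, 20% reads as 22-33% and 40% as 43-57%. The documents cannot fix the true size, and it may be small. A bias from consent or from the timing of the approach, possibly in the opposite direction, remains conditional, as does any effect on length of stay. The net direction is therefore unknown. This should be changed before the pilot starts, but it does not invalidate the design.

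**What to change.** For the pre-post comparison, count eligible patients and referrals in both periods with one chart-based rule applied to the full schedule of both clinics:

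- Use only items documented before the referral decision: age, listed comorbid conditions, a charted cognitive or functional diagnosis, and recorded weight loss. Patients never referred have no referral date, so the initial surgical consultation could serve as the common cut-off.
- Count every eligible patient regardless of consent, through aggregate counts or a waiver.
- Derive the per-surgeon referral percentages for adoption from the same counts.
- Report reach from the staff-screened denominator, including suspected cases, as a secondary post-period result.
- State when the study approach occurs relative to referral, and whether baseline patients give consent.

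The cost is a short abstraction algorithm and one request to the ethics board, whose Phase 3 approval is still pending in the article. The chart-only rule misses some suspected cases, so the comparison describes a somewhat narrower population than the stated criteria, but the same rule applies in both periods. If the package changes what clinics document before referral, capture could still shift, and this should be noted when reporting.
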